## Date management

7

The data administrator will design a case report form (CRF) based on the research plan and set logical verification according to the data verification plan (DVP). After passing the test and obtaining approval from the researchers, the case report will be released for further use. Data entry personnel shall input information in a timely manner into the data management system according to the CRF completion instructions. After data entry, the researcher will review and sign. After the principal researchers, the statistician and data administrator shall jointly sign the “Database Lock Record,” the data administrator will lock the database and submit it to the statistician. After the statistical analysis is completed, the data administrator will close the database.

## Statistical analysis

8

An independent statistician will perform the full analysis set (FAS), per protocol set (PPS), and safety analysis set (SS). FAS is used to analyze data collected from patients randomized in the trial and treated at least once. PPS is performed in cases that complete all steps of the experimental protocol. SS is performed to analyze the data collected from subjects who receive at least one treatment and have a record of safety indicators. The number of cases in the SS will be determined as the denominator to calculate the incidence of AEs and SAEs.

Descriptive statistical results will be shown as mean ± standard deviation for continuous data, and as numbers and percentages for categorical data. Chi-square or Fisher’s exact tests shall be used for categorical data and independent t-tests or rank-sum tests for continuous data, depending on whether the data meet the normal distribution and homogeneity of variance. *p* < 0.05 will be considered to indicate a statistically significant difference.

For safety evaluation, the proportions of AEs and SAEs will be calculated using chi-square or Fisher’s exact tests. We will perform a paired t-test or rank-sum test to compare differences in vital signs and laboratory test results during the screening period and at the end of the intervention.

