### Study design and setting

2.1

This study will be a randomized, double-blind, placebo-controlled multicenter clinical trial designed to evaluate the efficacy and safety of IFN-α1b injection into the foramen in patients with PHN. This study will be performed at 11 hospitals in China: China-Japan Friendship Hospital, First Affiliated Hospital of Chongqing Medical University, CR & WISCO General Hospital, Second Affiliated Hospital of Guangzhou Medical University, First Hospital of Lanzhou University, First Affiliated Hospital of Xiamen University, Affiliated Hospital of Xuzhou Medical University, Yanbian University Hospital, Nanjing Drum Tower Hospital, Jilin Provincial People’s Hospital, and Gansu Provincial Hospital. Two-hundred participants who meet the inclusion criteria but not the exclusion criteria will be randomly divided into treatment and control groups in a 1:1 ratio. The study will include a baseline period, a 2-week treatment, and a 3-month follow-up after enrollment. Individual researchers will screen subjects who meet the inclusion criteria. Subjects who do not meet the exclusion criteria will be included in this study. Collection of baseline information will be completed through case report form (CRF) during the baseline period. The experimental flowchart is shown in Figure 1 by Figdraw. The schedules for enrollment, intervention, and assessment are listed in Table 1.

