**Figure 1 fig1:**
[figure not shown]
Flowchart of the experimental: efficacy and safety of ultrasound-guided injection of interferon-alpha1b (IFN-alpha1b) into foramen of patients with postherpetic neuralgia.

**Table 1 tab1:** Schedule of enrolment, treatments, and assessments.

Procedure	Screening period	Treatment period		Follow-up period		
	Visit 1	Visit 2	Visit 3	Visit 4	Visit 5	Visit 6
	Day −3 to 0	Day 7 (After 2 treatments)	Day 14 (After 4 treatments)	Day 30 after treatment	Day 60 after treatment	Day 90 after treatment
Enrolment						
Informed consent	•					
Demographic information	•					
Vital sign	•	•	•	•	•	•
Physical examination	•	•	•	•	•	•
Imaging test	•					
ECG	•					
Laboratory test	•		•			
Randomization	•					
Intervention						
Treatment group		Inject interferon into intervertebral foramen 2 times per week				
Control group		placebo interferon into intervertebral foramen 2 times per week				
Assessment						
VAS	•	•	•	•	•	•
Duration of pain relief	•	•	•	•	•	•
SF-36	•	•	•	•	•	•
Virus load of VZV DNA	•		•			
humoral cytokine level	•		•			
Drug consumption	•	•	•	•	•	•
Adverse events		•	•	•	•	•

ECG, electrocardiogram; VAS, visual analogue scale; SF-36, 36-item short-form; VZV, varicella-zoster virus. Indicate completion or inclusion of the content.

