### Sample size

2.2

A preliminary study with a small sample size and ≥ 25% reduction in VAS after one treatment as the primary outcome showed that the response rate was 46% in the treatment group and 23% in the control group. With *α* = 0.05 (bilateral) and power = 0.90, PASS17 software suggested that at least 85 subjects should be included in each group. Assuming a loss to follow-up rate of 15%, the adjusted sample size should be 100.

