### Randomization and blinding

2.6

A statistician who does not participate in this trial will perform randomization. Random codes will be generated by SAS software using stratified block randomization. Randomization numbers will be assigned by the data analysis system for the Interactive Web Response System (DAS for IWRS).

Drug blinding will be performed by personnel from the statistical unit. A packer unrelated to the study will repackage IFN and placebo according to the drug packaging number, verification code, and the corresponding group generated by the SAS software. The investigational drug for each participant is packaged separately. The blinding process will be recorded and preserved.

All the individuals involved in the trial will be blinded to the treatment assignment until the end of the study. This study will be unblinded after the data-auditing report is completed, and the database is locked. The unblinded document will be signed jointly by the main researchers and statisticians.

Emergency letters shall be provided for emergency unblinding, and each random number corresponds to an emergency letter. If researchers consider that blinding hinders the management of AEs, emergency unblinding will be allowed.

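### The VAS primary outcome is tested without adjustment for baseline VAS or the randomisation strata, and the choice between a mean-based and a rank-based test waits for the trial data; the cost is precision and a fixed effect measure, not false positives

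*Protocol article*

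**What the plan says.** Section 8 of the protocol article assigns "independent t-tests or rank-sum tests for continuous data, depending on whether the data meet the normal distribution and homogeneity of variance". It does not treat the primary outcomes separately, and no covariate, stratum, centre effect or regression model appears anywhere in the article.

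Section 5.1 names two primary outcomes, the VAS score on a 100 mm line and the duration of pain relief in days. Both are numerical, so the Section 8 rule reaches both. Pretreatment VAS enters only through the pain relief rate, which defines a day of relief.

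Table 1 schedules VAS at screening and at five later visits. Section 2.3 makes a screening VAS an entry condition, so every randomised patient has a baseline value.

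Section 2.6 says: "Random codes will be generated by SAS software using stratified block randomization". The stratification factors are not named. Section 2.1 lists 11 hospitals.

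Section 2.2 sizes the trial on a responder proportion: "the response rate was 46% in the treatment group and 23% in the control group".

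**The concern.** The article does not leave this choice to an analysis plan. It names the tests and the rule for choosing between them, so an analysis plan that follows it inherits the choice. There are two weaknesses.

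- **The effect measure is not fixed.** A t-test compares means. A rank-sum test compares distributions through ranks. Normality and variance checks on the trial data decide which one is used, so the quantity reported for a primary outcome is settled only after the data are in hand.
- **Available information is not used.** Baseline VAS usually predicts later VAS, and adjusting for it narrows the confidence interval without another patient. Stratified randomisation balances the arms on the strata, but an unadjusted test takes no credit for that balance.

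At stake are the width of the interval for the VAS effect, the chance of detecting a real effect, and a reader's ability to know in advance what is being estimated.

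**Working it through.** **1. The plan's own figure.** The inputs from Section 2.2 are 46% and 23%, two-sided alpha 0.05 and power 0.90. The unpooled normal formula gives

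n = (1.960 + 1.282)² × (0.46×0.54 + 0.23×0.77) / 0.23² = 10.507 × (0.2484 + 0.1771) / 0.0529 = 84.5, so 85 per arm.

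This matches "power = 0.90, PASS17 software suggested that at least 85 subjects should be included in each group". With 15% loss, 85/0.85 = 100 per arm, which matches "Assuming a loss to follow-up rate of 15%, the adjusted sample size should be 100". The calculation uses a proportion and involves neither a VAS SD nor a correlation. Nothing below alters it.

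**2. Variance removed by baseline adjustment.** The documents give no baseline-to-follow-up correlation r, so r = 0.3 to 0.7 is an assumption. Relative to raw follow-up VAS, the residual variance is 1 − r². Relative to change from baseline, the ratio is (1 − r²)/(2 − 2r) = (1 + r)/2.

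| r (assumed) | Residual variance vs raw VAS | Cut vs raw VAS | Cut vs change score |
|---|---|---|---|
| 0.3 | 0.91 | 9% | 35% |
| 0.5 | 0.75 | 25% | 25% |
| 0.7 | 0.51 | 49% | 15% |

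The article does not say whether raw or change values are compared. Adjustment gains under either reading.

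**3. Power at 85 per arm.** A difference of 0.40 SD is also an assumption. Adjustment turns it into 0.40/√(1 − r²) residual SDs. Two-sample t-test power, two-sided 5%:

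| Analysis | Effective standardised difference | Power |
|---|---|---|
| Unadjusted, raw VAS | 0.400 | 73.7% |
| Adjusted, r = 0.3 | 0.419 | 77.6% |
| Adjusted, r = 0.5 | 0.462 | 84.9% |
| Adjusted, r = 0.7 | 0.560 | 95.3% |

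In patients: for a difference that needs 85 per arm unadjusted, the adjusted analysis needs 78 (r = 0.3), 64 (r = 0.5) or 44 (r = 0.7) per arm.

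**4. Strata.** If the strata explain a share f of VAS variance and the arms are perfectly balanced within them, the unadjusted test's true size is 2 × [1 − Φ(1.96/√(1 − f))]. For f = 0.10 (assumed), 1.96/√0.90 = 2.066 and the size is 3.9%. A simulation with 11 equal site strata of 16 patients and a 10% site share gave 4.1% to 4.4%. In the same simulations with a 0.40 SD effect, r from 0.3 to 0.7 and a site share from 0 to 0.10, power was about 74% to 77% unadjusted and 78% to 99% adjusted for baseline and site.

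**5. Does pre-testing inflate false positives?** Choosing between the t-test and the rank-sum test by Shapiro and Levene checks at 85 per arm gave a simulated type I error of 5.2% for normal data and 5.1% for exponential data (10,000 runs each). There is no material inflation under these shapes.

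**The case against.** The strongest reply is that an unadjusted two-sample test is valid under randomisation, that no type I error harm is shown, and that the size of the loss rests on figures the documents do not contain. All three parts stand. The entry threshold on VAS also truncates the baseline and may weaken its correlation with follow-up, which is why the range starts at r = 0.3, where the gain is modest. The 0.40 SD difference is illustrative and is not the effect for which the trial was sized.

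A reader might infer more than the article supports:

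- **That data-dependent test choice inflates false positives.** The simulations do not show it. The open effect measure is the problem.
- **That arms are compared visit by visit, with patients dropping out of each test.** Section 8 names no visit, and Section 5.1 says only that the outcomes are evaluated throughout the study. Visit-wise testing is one possible application. Missing-data handling may lie in a document not shown.
- **That baseline is ignored for both primary outcomes.** Duration of relief is defined relative to pretreatment VAS. The baseline point applies to the VAS score.
- **That the standard errors are certainly too wide because of the strata.** This holds only if the unnamed factors are prognostic.
- **That the sample size is wrong.** It reproduces, and it rests on a different quantity.

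None of this removes the core point: the stated rule leaves the VAS effect measure open and makes no covariate use of baseline VAS or the strata.

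**Conclusion.** The point holds as a recommended improvement, not as a threat to validity. For the VAS score, Section 8 leaves the effect measure to be settled by the data and forgoes precision that costs nothing to obtain. Under an assumed correlation of 0.3 to 0.7, the variance forgone against raw follow-up VAS is 9% to 49%. At 85 per arm and an assumed 0.40 SD difference, power is about 74% instead of 78% to 95%. If the strata explain 10% of VAS variance (assumed), the nominal 5% test runs at about 4%. The direction of these losses is secure if baseline VAS and the strata are prognostic. Their size is not known from the documents.

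**What to change.** In Section 8, and in the analysis plan:

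- **VAS score.** Replace the data-dependent test with one prespecified model, either ANCOVA at a single named time point or a mixed model for repeated measures. Include baseline VAS and the randomisation stratification factors as covariates. The article names neither a primary time point nor the factors, so both must be stated. If site is a factor, 200 patients over 11 hospitals is about 18 each; use random site effects or pool small sites by a rule set in advance. Report the adjusted mean difference with its 95% CI, and keep the rank-sum test as a sensitivity analysis.
- **SF-36 and other continuous outcomes measured at baseline.** Adjust each for its own baseline value, not baseline VAS, and for the strata.
- **Duration of pain relief.** Prespecify one test that accounts for the strata, for example a stratified rank-sum (van Elteren) test.

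The cost is wording and slightly more programming, completed before unblinding. No new data, visits or patients are needed, and the sample size stays as stated.

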**Conclusion:**

This study is expected to provide evidence for the efficacy and safety of IFN-α1b injection into the intervertebral foramen in patients with PHN.

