## Safety evaluation

6

In this trial, vital signs, electrocardiogram (ECG), hematology tests (differential count of white blood cells, neutrophils, lymphocytes, monocytes, red blood cells, and platelets), urinalysis (PH, protein, specific gravity, red blood cell microscopy, and white blood cell microscopy), and tests for blood chemical values (creatinine, urea, albumin, total bilirubin, direct bilirubin, ALT, and AST) will be conducted before and after treatment. If AEs or SAEs occur during participation, the symptoms, onset, duration, severity, relationship to the intervention, actions taken, and outcomes will be recorded in detail. Possible adverse reactions related to the treatment include fever, vomiting, nausea, granulocytopenia, thrombocytopenia, abnormal electrocardiogram, and rash. The incidence rates of AEs and SAEs will be determined.

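### The only stated comparison of adverse events is a significance test at p < 0.05, which says little about safety when the excess is uncommon or modest; report risk differences with confidence intervals instead (minor)

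*Protocol article*

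**What the plan says.** Safety stands beside efficacy as an aim. The abstract's conclusion reads: "This study is expected to provide evidence for the efficacy and safety of IFN-α1b injection into the intervertebral foramen in patients with PHN".

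The safety paragraph of section 8 (Statistical analysis) describes two analyses:

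- For events: "For safety evaluation, the proportions of AEs and SAEs will be calculated using chi-square or Fisher’s exact tests".
- For vital signs and laboratory results: a paired comparison of screening with the end of the intervention. As worded, this is before against after, not arm against arm.

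The general rule of the same section is that p "< 0.05 will be considered to indicate a statistically significant difference". The safety set, which requires one treatment and a safety record, supplies the denominator for AE and SAE incidence.

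Section 6 (Safety evaluation) says that incidence rates will be determined and lists what is expected, without rates: "Possible adverse reactions related to the treatment include fever, vomiting, nausea, granulocytopenia, thrombocytopenia, abnormal electrocardiogram, and rash".

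Section 2.2 (Sample size) rests on an efficacy response only: "the response rate was 46% in the treatment group and 23% in the control group".

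**The concern.** Two things are wrong with the AE/SAE sentence.

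First, it is incorrect as written. Proportions are estimated from counts and a denominator. A chi-square or Fisher test yields a p-value for the hypothesis that two proportions are equal. The sentence names the test where the estimate belongs.

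Second, the tool does not suit the aim. For efficacy, the favourable result is a rejected null hypothesis, and the sample size protects against missing a true effect. For safety, the favourable result is the absence of a relevant excess. A test that fails to reject cannot show this unless it had good power against the excess that matters. What answers the question is the size of the difference between arms and how large an excess the data still allow. The section names neither.

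At stake is how much the safety result can carry. If the p-value is the only comparison, a non-significant difference in an uncommon reaction or in SAEs is the expected result whether or not IFN-α1b causes a modest excess.

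**Working it through.** **Inputs**

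- From section 2.2: response rates 0.46 and 0.23, two-sided α = 0.05, power 0.90, 85 per group, 15% loss, 100 per group.
- From section 2.1: 200 participants, 1:1.
- From section 8: chi-square or Fisher test, threshold 0.05, safety set as denominator.
- Assumed: all AE rates, because the article gives none. A range is shown.

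**Step 1. Reproduce the plan's own figure.** The plan states "0.05 (bilateral) and power = 0.90, PASS17 software suggested that at least 85 subjects should be included in each group". With the unpooled normal approximation,

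n = (z₀.₉₇₅ + z₀.₉₀)² × [p₁(1−p₁) + p₂(1−p₂)] / (p₁−p₂)²
= (1.960 + 1.282)² × (0.46×0.54 + 0.23×0.77) / 0.23²
= 10.507 × (0.2484 + 0.1771) / 0.0529 = 84.5, so 85.

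Allowing for loss: 85 / (1 − 0.15) = 100 per group. The figure holds. It contains no safety quantity.

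**Step 2. Choose the safety denominator.** I use 100 per arm. The 85 is an efficacy number net of loss to follow-up. It does not fit a safety set in which a participant stays after one treatment and one safety record.

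**Step 3. Chance of missing a true excess.** For assumed rates p_C (placebo) and p_I (IFN), sum over all pairs of counts:

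miss = 1 − Σₐ Σ_b Bin(a; 100, p_I) × Bin(b; 100, p_C) × 1[two-sided p < 0.05 and a > b].

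The test is Fisher when the smaller expected count is below 5 and uncorrected chi-square otherwise. The last two columns apply one test throughout.

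| Placebo v IFN | Missed, test chosen by expected count | Fisher only | Chi-square only |
|---|---|---|---|
| 1% v 3% | 97% | 97% | 86% |
| 1% v 5% | 80% | 81% | 63% |
| 2% v 6% | 80% | 83% | 72% |
| 2% v 8% | 57% | 63% | 51% |
| 5% v 10% | 73% | 81% | 73% |
| 20% v 30% | 63% | 69% | 63% |
| 10% v 20% | 48% | 56% | 48% |
| 5% v 15% | 32% | 41% | 32% |
| 10% v 25% | 18% | 24% | 18% |
| 20% v 40% | 12% | 16% | 12% |
| 5% v 20% | 8% | 12% | 8% |

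The first six rows are missed more often than found. The last four are found more often than missed, and 10% v 20% is close to even.

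**Step 4. What an interval would add.** These are illustrative counts out of 100 per arm, IFN first, with Newcombe 95% intervals for the risk difference.

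| Events | Fisher p | Difference (95% CI), percentage points |
|---|---|---|
| 3 v 1 | 0.62 | 2.0 (−2.9 to 7.5) |
| 10 v 5 | 0.28 | 5.0 (−2.6 to 13.0) |
| 20 v 20 | 1.00 | 0.0 (−11.1 to 11.1) |
| 7 v 1 | 0.065 | 6.0 (0.3 to 12.8) |

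In the first three rows the p-value is far from 0.05, yet the data still allow an excess of about 7 to 13 points. The 7 v 1 row is a borderline case: uncorrected chi-square gives p = 0.030, so it shows the conservatism of Fisher's test more than a general failure. Even no events in 100 on IFN leaves a one-sided 95% upper limit of 1 − 0.05^(1/100) = 3.0% for that arm.

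**The case against.** The strongest reply is that the defect is not in the text. Given a safety aim and a single test, a reader might infer that a non-significant result will be presented as evidence of safety. No sentence says so. Section 8 defines what p < 0.05 means and gives p ≥ 0.05 no meaning, and the abstract says only that evidence is expected. This reply stands, and the point does not rest on that inference.

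A reader might also infer that the test is the only between-arm safety information. The article does not support this. Incidence will be determined on the safety set, and categorical data will be shown as numbers and percentages, so anyone with counts by arm can derive a risk difference and its interval. The general rule for continuous data, independent t-tests or rank-sum tests, is not limited to efficacy and could cover laboratory values between arms.

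A third tempting reading is that relevant harms would be missed most of the time. The working does not bear that out in general: 5% v 15% is found in about two trials of three and 5% v 20% in more than nine of ten. The article also does not define a relevant excess.

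Finally, this is a condensed article, and the form of safety summaries is commonly left to the full protocol or the analysis plan. A missing interval alone would be no finding, and sizing on efficacy alone is ordinary. What remains is that section 8 does not leave the matter open. It names the method, words it wrongly, and names one that suits the aim less well than an equally simple alternative.

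**Conclusion.** The point holds in a narrow form and is minor. The AE/SAE sentence confuses estimating a proportion with testing a difference, and it makes a significance test the only stated AE/SAE comparison in a trial with a safety aim.

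At 100 per arm, a non-significant result says little about excesses of about 4 to 5 points from base rates of 1% to 5% (missed in 73% to 80% of trials). It says more about large ones, such as 5% v 20% (missed in 8%).

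These sizes rest on assumed event rates, on 100 analysed per arm, and on Fisher's test for small expected counts with uncorrected chi-square otherwise. Using Fisher throughout raises the miss rates, and using chi-square throughout lowers those for rare events. No stated figure in the protocol is in error: the sample size reproduces.

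**What to change.** Replace the AE/SAE sentence in section 8 with:

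> AE and SAE incidence in the safety set, and the incidence of each reaction listed in section 6, will be summarised by arm with the risk difference (IFN minus placebo) and its 95% confidence interval (Newcombe or exact). Chi-square or Fisher p-values are descriptive, and p ≥ 0.05 will not be interpreted as evidence of safety.

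The cost is this wording and a few extra columns in the safety tables. No patients, visits or tests are added. The change adds no power: intervals for uncommon events will be wide, so the safety conclusion becomes more modest.

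### The only analysis named for laboratory and vital-sign safety is a before/after test, which cannot isolate the interferon effect, and its rank-sum fallback, read literally, ignores the pairing

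*Protocol article*

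**What the plan says.** The safety paragraph of the Statistical analysis section (section 8) gives vital signs and laboratory results one analysis of their own: "We will perform a paired t-test or rank-sum test to compare differences in vital signs and laboratory test results during the screening period" and the end of the intervention. The two time points are thus "during the screening period and at the end of the intervention", in the same patients. The Safety evaluation section (section 6) matches this: the measurements "will be conducted before and after treatment". Neither place mentions a comparison of these values, or of their changes, between interferon and placebo.

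Two other sentences in section 8 bear on the point:

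- For continuous data in general, the plan is "independent t-tests or rank-sum tests for continuous data". Here the rank-sum test stands as the alternative to the independent t-test.
- For events, "the proportions of AEs and SAEs will be calculated using chi-square or Fisher’s exact tests".

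The design is placebo-controlled, and patients "will be randomly divided into treatment and control groups in a 1:1 ratio". Under Intervention (section 3), both arms receive lidocaine in the injection and oral pregabalin.

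**The concern.** There are two separate problems.

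**The comparator.** A before/after change within patients combines any interferon effect with everything else that happens over the two weeks: lidocaine, pregabalin, regression to the mean and time. Only the difference between the randomised arms removes what they share. Finding significance in one arm and not in the other does not test that difference. The sentence also does not say whether the paired test is run per arm or on all patients together. If it is run on all patients, a shift confined to the interferon arm is halved by the 1:1 allocation.

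**The fallback test.** The rank-sum test is for two independent samples. Applied to screening and end-of-treatment values of the same patients, it uses a variance that is too large when those values are positively correlated. It then rejects too rarely.

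Safety is half of the stated aim, and section 6 anticipates haematological harm: "Possible adverse reactions related to the treatment include fever, vomiting, nausea, granulocytopenia, thrombocytopenia, abnormal electrocardiogram, and rash". The laboratory analysis bears directly on this.

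**Working it through.** **Inputs.** The article gives no figure for this analysis. The one number taken from it is 100 patients per arm, which reproduces from the Sample size section (46% v 23%, two-sided α 0.05, power 0.90):

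- n = (1.960 + 1.282)² × (0.46×0.54 + 0.23×0.77) / 0.23² = 84.5, so 85
- 85 / 0.85 = 100

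The rest is assumed, because the article is silent: before/after correlation ρ from 0.3 to 0.7, normal values with SD 1 at both times, and shifts of 0.2 to 0.4 SD.

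**Step 1: within-arm test when there is no interferon effect.** Suppose both arms shift by the same amount, with ρ = 0.7.

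- SD of change = √(2(1 − 0.7)) = 0.775; standard error with 100 patients = 0.0775
- Probability of a significant paired test ≈ Φ(shift/0.0775 − 1.96)

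| Common shift (SD) | shift/SE | P(significant within one arm) |
|---|---|---|
| 0.2 | 2.58 | 0.73 |
| 0.3 | 3.87 | 0.97 |
| 0.4 | 5.16 | 0.999 |

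A between-arm comparison of change would be significant with probability 0.05 in every row, because the expected changes are equal.

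**Step 2: level of the rank-sum test on paired values.** In large samples the true variance of the rank-sum statistic is its independent-sample variance times f = 1 − (6/π)·asin(ρ/2). The actual two-sided level is 2[1 − Φ(1.96/√f)].

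| ρ | f | 1.96/√f | Level, formula | Level, simulated |
|---|---|---|---|---|
| 0.3 | 0.712 | 2.32 | 0.020 | 0.021 |
| 0.5 | 0.517 | 2.72 | 0.006 | 0.005 |
| 0.7 | 0.317 | 3.48 | 0.0005 | 0.0007 |

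The simulation used 3,000 runs of 100 pairs. In the same runs the signed-rank test rejected between 0.036 and 0.051 of the time.

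**Step 3: power for a 0.3 SD shift, same simulation.**

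| ρ | Rank-sum | Signed-rank | Paired t |
|---|---|---|---|
| 0.3 | 0.55 | 0.69 | 0.72 |
| 0.5 | 0.56 | 0.82 | 0.84 |
| 0.7 | 0.57 | 0.96 | 0.97 |

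**Step 4: what a between-arm analysis would deliver.** Take a 0.3 SD shift in the interferon arm only, ρ = 0.7, and 100 per arm.

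- Change scores: SE = √(2×0.6/100) = 0.110; power ≈ Φ(0.3/0.110 − 1.96) ≈ 0.78
- Adjusted for the screening value: SE = √(2×(1 − 0.7²)/100) = 0.101; power ≈ Φ(0.3/0.101 − 1.96) ≈ 0.84

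This is less than the within-arm paired test (0.97), because two arms contribute variance. The within-arm figure, however, is power to detect any change from any cause (step 1).

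**The case against.** The strongest case on the other side has four parts.

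**Other sentences use the placebo arm.** A reader might infer that the placebo arm plays no part in the safety analysis. The article does not support that. The general sentence on independent tests is not confined to efficacy, and laboratory values are continuous data, so an arm comparison is not excluded. The test of adverse-event proportions is naturally read as arm against arm, and a cytopenia recorded as an adverse event would enter it. The Drop-out criteria also set platelet and neutrophil limits for individual patients, so noticing a severe fall does not depend on a p-value. All of this stands. It leaves open continuous shifts that are not recorded as events, for which the specific sentence names only the before/after test.

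**Attribution is not stated.** The article does not say that before/after changes will be ascribed to interferon. That is so. The point is that the named analysis could not support such a statement if one were made.

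**Rank-sum may be loose wording.** It stands beside a paired t-test, so pairing is plainly intended and signed-rank may be what is meant. If so, steps 2 and 3 describe a test that will never be run, and one word needs changing. Against this, section 8 also uses the term for independent samples, so the literal reading is open.

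**The sizes are assumed.** The correlations and shifts are not in the article. Nor does it say that the laboratory values are skewed, so how often the fallback would be used is unknown. This limits the figures. The direction of the error in the level holds for any positive before/after correlation.

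**Conclusion.** The point holds in a limited form. The one analysis named for laboratory and vital-sign safety compares patients with themselves. It cannot separate interferon from changes shared by both arms: with 100 per arm and ρ = 0.7, a shared shift of 0.2 to 0.4 SD is declared significant within an arm with probability 0.73 to 0.999.

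Read literally, the fallback errs toward too few rejections and would tend to miss a shift rather than raise a false alarm. It is a naming correction if signed-rank was intended; the comparator problem remains either way.

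A reader might rate this as an essential correction. The documents do not support that: it is a supporting safety analysis, and the primary outcomes, sample size, randomisation and adverse-event incidence are untouched. It should be fixed.

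**What to change.** Two changes in section 8:

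1. Make a between-arm comparison the stated analysis for vital signs and laboratory results: either the change from screening, or the end-of-intervention value adjusted for the screening value, with the difference and its 95% confidence interval. A rank-sum test is valid here if applied to change scores between arms.
2. Label any within-arm before/after test as descriptive, say that it is done per arm, and name the Wilcoxon signed-rank test as its non-parametric alternative.

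The cost is two sentences. The data, visits and sample size stay the same. Shift tables by arm would be useful but are optional detail for the statistical analysis plan.
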